## Abstract

**Background:**

An important condition for independent living is having a well-functioning social network to provide support. An Integrated Neighbourhood Approach (INA) creates a supportive environment for the frail elderly, offering them tailored care in their local context that allows them to improve self-management abilities and well-being. The purpose of our research is to investigate how an INA can contribute to outcomes of frail elderly and the cost-effectiveness of such a program. The first central study question is: To what extent does INA contribute to (a) continuous, demand-driven, coordinated care and support for the independently- living frail elderly; (b) improvement of their well-being and self-management abilities; and (c) reinforcement of their neighbourhood networks. The second central research question is: is the INA a cost-effective method to support the frail, independently- living elderly?

**Methods:**

We investigate a Dutch INA. This transition experiment aims to facilitate the independently-living frail elderly (70+) to live the life they wish to live and improve their well-being. The study population consists of independently-living frail elderly persons in Rotterdam. The transition experiment starts in two Rotterdam districts and is later extended to two other districts. We propose a concurrent mixed methods design, that is, a combination of qualitative and quantitative research methods to evaluate processes, effects and costs of INA. Such a design will provide insight into an on-going INA and demonstrate which of its elements are potentially (cost)-effective for the frail elderly.

**Discussion:**

We embrace a wide range of scientific methodologies to evaluate the INA project and obtain information on mechanisms and contexts that will be valuable for decision making on local and national levels. The study will lead to a better understanding of how to provide support via social networks for the frail elderly and add to the knowledge on the feasibility and cost-effectiveness of the program in maintaining or improving their well-being. Last, the study will highlight the factors that determine the program's success or failure.

## Background

People with highly-functioning social networks are better able to give and receive support, are more psychologically resilient, and live longer and healthier lives [1]. Regrettably, various reports and signals from the field suggest that the current professional approach fails to provide frail elderly people with needed social support networks to make living conditions safer, more stimulating, comfortable, and pleasant and to enable them to live in their own neighbourhoods for a longer time. Strengthening social networks fosters early detection of problems, is crucial to public health, and is expected to reduce the pressure on the healthcare system by preventing or delaying nursing home admissions. Facilitating elderly people through an Integrated Neighbourhood Approach (INA) to live independently for as long as possible requires a supportive community environment, which is in turn dependent on the presence of meeting places [2], mutual interdependence of residents, and motivation to invest in local relationships reflected, for example, by residential stability [3]. Neighbourhood differences in this regard have been reported. An important condition seems to be that the community engage in shared activities, thus establishing contacts through which social networks can develop [4,5]. Residents will be more inclined to participate in neighbourhood activities if they perceive a sense of community [6]. Currently, the frail elderly have to depend on professional care; informal networks and social support are underemployed [7].

The point of departure of INA is reinforcing networks between welfare, health care, informal care and community members in neighbourhoods, optimizing current services, and involving the (frail) elderly. Such a demand-driven approach offers elderly people tailored care - including care-related services such as housing - in their local context to enhance self-management abilities and well-being. The focus is on "de-medicalisation" and recognition of mutual dependence between welfare, health care, and informal care. Thus, for INA to be successful the partners in primary, secondary, and tertiary care as well as informal networks need to work well together - from signalling problems to prevention, cure, care, promotion of welfare, and independent living. Early recognition of complaints and encouraging effective self-management may positively influence well-being. It requires the elderly to 'star' in the 'production' of their own well-being as a form of empowerment [8]. Informal caregivers play a central role in their social networks and are important to supporting independent living. Evidence suggests that caring for a frail elderly person is an arduous task that may cause financial difficulties, emotional strain, or physical problems [9,10]. A supportive network for elderly may alleviate such negative aspects of caregiving, which in turn helps sustain informal caregivers' support.

While INA may improve outcomes, evidence regarding the (cost-) effectiveness of such programmes is lacking. The purpose of our research is to investigate how an INA can contribute to outcomes of the frail elderly and its cost-effectiveness. The first central study question is: To what extent does INA contribute to (a) continuous, demand-driven, coordinated care and support for the independently- living frail elderly and the well-being of their informal caregivers; (b) improvement of their well-being and self-management abilities; and (c) reinforcement of their neighbourhood networks. The second central research question is: is the INA a cost-effective method to support the frail, independently- living elderly?

## Methods

### 

#### Setting: Dutch example of an Integrated Network Approach

Although welfare and health care are widely available in the city of Rotterdam, the specific needs of frail elderly remain inadequately addressed and 'outreach' work is lacking. A number of 'best practices' may exist locally, but not a good overview of the services because of fragmentation and compartmentalisation. Such services are difficult for the elderly to find and are not visible to others in the city. In the current situation the frail elderly have to depend on professional care, while informal networks and social support are underused. An INA is based on reinforcing neighbourhood networks through which continuous, demand-driven, coordinated care and support can eventually be offered to all independently-living frail elderly persons. Community workers - professionals with a care or welfare background familiar with the residential area - are important to the network. They visit the elderly at home and map their wishes and needs via a phased interview. In consultation with the elderly, they seek appropriate solutions within the (preferably informal) network. Such a transition experiment aims to facilitate independently-living frail elderly persons (70+) to live the life they wish to live, improving their well-being. The study population consists of independently-living frail elderly persons and their informal caregivers in Rotterdam. The transition experiment begins in two Rotterdam districts (*Lage Land/Prinsenland *and *Lombardijen) *and is later extended to the *Oude Westen *and *Vreewijk *districts.

The project ('An integrated neighbourhood approach to welfare and care for the frail elderly in Rotterdam') and the associated evaluation study are part of the National Care for the Elderly Programme (NPO) launched in the Netherlands in 2008. Funding is provided by the Netherlands Organisation for Health Research and Development (ZonMw; project number 314030201).

#### Evaluation design

Our evaluation study uses a concurrent mixed-methods design (a combination of qualitative and quantitative research methods) to evaluate processes, effects and costs of INA. A frequent shortcoming of evaluation studies is failure to give good descriptions of what was done and the context in which it was done [11]. In the first phase (months 1-6), therefore, the eventual local-level interventions will be described extensively along with how welfare, care, and network support for frail elderly persons and their informal caregivers is achieved. A good description of interventions is the first step and towards that, key figures including community workers will be interviewed.

The evaluation will comprise (I) inventory and (II) controlled pre-post measurement. Inventory is taken among the elderly (70+) in the four relevant districts (Lage Land/Prinsenland, Lombardijen, Oude Westen, and Vreewijk) to investigate the general situation of elderly in these districts. Furthermore, we investigate social networks, social cohesion, and the sense of community in these districts to learn if INA contributed not only to elderly included in the experiment, but to the wider context as well.

The controlled pre-post measurement is the main part of the evaluation. Independently-living elderly (70+) in the first two districts will serve as the experimental group (Figure 1).

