#### I. Inventory

A sample of 1440 independently-living elderly (70+) in the four districts will be taken from the population register, 430 eligible elderly per district and proportional to neighbourhood and age. The eligible elderly will be asked by mail to complete a (written or online) questionnaire (T0) whose estimated completion time is 15 minutes. Those who do so will be rewarded with a 1/5 ticket in the monthly Dutch State lottery. Those who do not respond after having been sent a reminder will be telephoned. If not available, they will be visited at home. This strategy is expected to result in a 60% response rate (n = 864). The group will be contacted again after 24 months (T1) to assess whether (i) local social networks have been reinforced, (ii) the elderly participate more actively, and (iii) the frail elderly have built up better personal networks. Using the same strategy as in the T0 measurement (incentives and follow-ups), we expect a 70% response at T1 (which includes a 15% attrition from death, relocation, institutional admission, et cetera), resulting in n = 605.

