#### II. Controlled pre-post measurement (effect evaluation)

The independently-living elderly (70+) in the first two districts whose TFI-score is ≥ 5 [12] will serve as the experimental group and will be recruited by community workers. On the basis of TFI-score, age, and gender, they will be matched with the elderly recruited from comparable districts in Rotterdam as a control group. In total we expect to include 370 elderly (247 in the experimental group; 123 in the control group). All will be interviewed at home by experienced interviewers at three time-points: T0, T1 (6 months after inclusion), and T2 (12 months after inclusion). On average the interviews will take 60 minutes.

Informal caregivers will be interviewed twice by telephone for about 15 minutes each. They will be identified on the basis of the definition provided in the National Care for the Elderly Programme: those who provide structured care voluntarily and for free to people in their family, household, or social network with physical, mental or psychological disabilities. It involves providing more care than usual in personal relationship and consists of tasks that healthy people could normally do themselves.

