#### ii. Effects

Assessment of effectiveness will be in terms of reaching the frail elderly, improving their self-management abilities and well-being, and improving the well-being of their informal carers. Demographic data and outcome indicators - well-being, quality of life, self-management abilities, cognitive functioning, social networks, social cohesion, sense of community in the neighbourhood - will be captured with specific instruments (table 1).

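### The inventory is meant to show effects of INA beyond the people included in it, but as described it cannot tell INA recipients from other residents

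*Protocol article*

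**What the plan says.** The Evaluation design section gives the district-level measurement a purpose of its own, "to learn if INA contributed not only to elderly included in the experiment, but to the wider context as well".

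The section I. Inventory then fixes the sample: "A sample of 1440 independently-living elderly (70+) in the four districts will be taken from the population register". Follow-up comes two years later: "The group will be contacted again after 24 months (T1) to assess whether (i) local social networks have been reinforced". The other two questions at that contact are whether older people participate more actively and "iii) the frail elderly have built up better personal networks".

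The section II. Controlled pre-post measurement takes its intervention arm from the same age group in two of those four districts. People with a TFI score of 5 or more "will serve as the experimental group and will be recruited by community workers", and 247 are expected. The Setting section adds that INA is later extended to the other two inventory districts and is meant in time to be available to every frail older person living independently.

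The article describes the inventory's frame, stratification, incentive, reminders and expected response. It does not mention leaving out INA recipients, asking respondents about INA, or linking them to the Client Monitoring System named under Process.

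**The concern.** An aim that contrasts people included in INA with the wider context needs a way to tell the two apart. The inventory sample and the INA clientele come from the same population, so some respondents at 24 months may have received INA in person. A change averaged over all respondents then contains a direct effect (among recipients) and a possible spill-over effect (among everyone else). With no spill-over at all, the average would still move by the direct effect times the share of recipients.

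At stake is the answer to the wider-context aim and the district-level evidence on reinforced neighbourhood networks, which is part (c) of the first research question. The controlled comparison, which the article calls the main part of the evaluation, is not affected.

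The problem is distinct from the lack of a comparison district for the inventory. A comparison district would deal with the time trend, but direct and spill-over effects would stay mixed.

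**Working it through.** **Inputs from the article.** Sample of 1440, response of 60% at T0 and 70% at T1 (I. Inventory); 247 in the experimental group (II. Controlled pre-post measurement); 1 TFI point with SD 3.0 (Sample size).

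**Assumptions, not in the article.** A direct effect of d = 1/3 SD (1/3.0, borrowed from the sample size section); no spill-over; 2,000 to 10,000 residents aged 70+ in the first two districts; a T0-T1 correlation r of 0.4 to 0.8; respondents split evenly over the districts.

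**1. The plan's own sample flow.** 1440 × 0.60 = 864, and 864 × 0.70 = 604.8, so 605. Both reproduce. About half, 302, are in the first two districts. Separately, "430 eligible elderly per district and proportional to neighbourhood and age" does not fit: 4 × 430 = 1720, whereas 1440/4 = 360. The steps below use the 605.

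**2. Formula.** With recipient share p and no spill-over, the mean change is p × d. A two-sided 5% test of mean change needs about 1.96 × √(2(1 − r)/n) SD.

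**3. If the 247 are the only recipients.**
- With 2,000 residents: p = 247/2,000 = 12.4%, about 37 of 302 respondents; shift 0.124 × 1/3 = 0.041 SD.
- With 10,000 residents: p = 247/10,000 = 2.5%, about 7 of 302; shift 0.025 × 1/3 = 0.008 SD.
- Needed for significance with n = 302: 0.071 SD (r = 0.8) to 0.124 SD (r = 0.4).
- Averaged over all four districts, with no recipients in the other two, the shift halves to about 0.02 and 0.004 SD, against 0.050 to 0.087 SD needed with n = 605.

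**4. If coverage grows in all four districts (n = 605, no spill-over).** The last two columns give the chance of a significant whole-sample change.

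| Share of respondents who are recipients | Non-recipients left | Shift (SD) | Chance, r = 0.6 | Chance, r = 0.4 to 0.8 |
|---|---|---|---|---|
| 10% | 545 | 0.033 | 15% | 12 to 25% |
| 20% | 484 | 0.067 | 45% | 32 to 74% |
| 30% | 423 | 0.100 | 79% | 61 to 97% |
| 40% | 363 | 0.133 | 96% | 85 to 99.9% |

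**5. How far coverage could go.** If the mean of 4.7 and SD of 3.0 apply to residents aged 70+ in general, a normal approximation puts 46 to 53% of them at TFI 5 or more (cut at 5 or at 4.5). If all recipients are frail, 20% coverage means reaching about 38 to 43% of frail residents (0.20/0.53 to 0.20/0.46), and 30% means about 57 to 65%. That is high for 24 months, but it lies within INA's stated ambition.

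**The case against.** The strongest reply is that this is an argument from silence. A single questionnaire item or a link to client records is detail that a journal article often leaves out, the study design figure is not available here, and the Client Monitoring System exists. That stands in part. The full protocol may contain such a flag, and then the sponsor need only say so. What remains is that the article states the contrast as a purpose, describes the sample in detail, and gives nothing that would allow the contrast to be made.

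Three stronger readings are tempting, and the article does not support them.

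- A reader might infer that change among recipients is going to be reported as a neighbourhood effect. No section says so; the Data analysis section lists only general analyses, including subgroup analyses.
- A reader might treat the aim on the personal networks of frail people as a pure spill-over question. Assuming 3,000 to 6,000 residents and 30 to 40% frail, recipients would then be 247/(0.4 × 6,000) = 10% to 247/(0.3 × 3,000) = 27% of the frail in the first two districts. But that aim names frail older people in general, who are INA's target, so recipients belong in it. The population and frailty figures are also assumptions.
- The effects section says "Assessment of effectiveness will be in terms of reaching the frail elderly", and a reader might infer that reach has no denominator. It does not follow. Of the 370 in the controlled study, 123 are controls from other districts whom INA does not reach. Reach could be estimated from aggregate client counts and the frailty prevalence in the register sample. The article does not say whether the inventory includes the TFI, although the aim on frail people needs some measure of frailty.

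It is also fair that non-recipients are defined by something that happens after T0 and depends on frailty, so splitting on it can bring in selection. That stands and limits how the split may be read.

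**Conclusion.** The point holds as a mismatch between a stated purpose and the described sample: direct and spill-over effects cannot be distinguished in the inventory's T0-T1 change. Its size depends on a coverage figure that the article does not give. With only the 247 as recipients it is about 0.01 to 0.04 SD in the first two districts and too small to mislead. At roughly 20 to 30% coverage, a whole-sample change has about a 45 to 79% chance of being significant with no spill-over at all (r = 0.6). Both results rest on the borrowed 1/3 SD direct effect; the first also needs the assumed population range, the second the assumed correlation. This is an inexpensive improvement to a secondary component, not a flaw in the main comparison.

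**What to change.** Add one item to the T1 inventory questionnaire: has the respondent been visited by an INA community worker since T0? Linking to the Client Monitoring System is an alternative where consent allows. However, the Process section describes registration over 12 months, so a link may not cover the inventory's 24.

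Then:
- report the T0-T1 change for all respondents, and separately for recipients and non-recipients;
- keep recipients in the aim on frail people's personal networks;
- base any statement about the wider context on non-recipients, adjusted for T0 characteristics and presented as descriptive.

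The cost is one question, plus a smaller sample for the wider-context analysis (for example 545 of 605 at 10% recipients, 423 at 30%). Self-report over two years will misclassify some people. Exposure is hard to reconstruct once T1 has closed, so the item should be settled before then. The flag does not make the change attributable to INA: no comparison district is described for the inventory, and that needs its own answer.

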**Figure 1 F1:**
[figure not shown]
**Study design Integrated Neighborhood Approach**.

#### I. Inventory

A sample of 1440 independently-living elderly (70+) in the four districts will be taken from the population register, 430 eligible elderly per district and proportional to neighbourhood and age. The eligible elderly will be asked by mail to complete a (written or online) questionnaire (T0) whose estimated completion time is 15 minutes. Those who do so will be rewarded with a 1/5 ticket in the monthly Dutch State lottery. Those who do not respond after having been sent a reminder will be telephoned. If not available, they will be visited at home. This strategy is expected to result in a 60% response rate (n = 864). The group will be contacted again after 24 months (T1) to assess whether (i) local social networks have been reinforced, (ii) the elderly participate more actively, and (iii) the frail elderly have built up better personal networks. Using the same strategy as in the T0 measurement (incentives and follow-ups), we expect a 70% response at T1 (which includes a 15% attrition from death, relocation, institutional admission, et cetera), resulting in n = 605.

#### II. Controlled pre-post measurement (effect evaluation)

The independently-living elderly (70+) in the first two districts whose TFI-score is ≥ 5 [12] will serve as the experimental group and will be recruited by community workers. On the basis of TFI-score, age, and gender, they will be matched with the elderly recruited from comparable districts in Rotterdam as a control group. In total we expect to include 370 elderly (247 in the experimental group; 123 in the control group). All will be interviewed at home by experienced interviewers at three time-points: T0, T1 (6 months after inclusion), and T2 (12 months after inclusion). On average the interviews will take 60 minutes.

Informal caregivers will be interviewed twice by telephone for about 15 minutes each. They will be identified on the basis of the definition provided in the National Care for the Elderly Programme: those who provide structured care voluntarily and for free to people in their family, household, or social network with physical, mental or psychological disabilities. It involves providing more care than usual in personal relationship and consists of tasks that healthy people could normally do themselves.

#### Sample size

We will include 370 elderly (2/3 in intervention group, 1/3 in control group). We will try to limit sample losses by personal house visits, but expect a loss of about 27% (by death, moving, no longer wishing to participate, etc.) between T0 and T2, resulting in a final sample of 270. This number - 180 in the intervention group and 90 in the control group - is required to detect a 1-point improvement in TFI-score in the intervention group as compared with the control group at T2 (with mean TFI-score 4.7, sd 3.0; one-sided test; alpha = 0.05, power = 0.80) [12].

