#### iii. Costs

A cost-effectiveness evaluation will be performed to determine whether INA is a cost-effective method to support the frail, independently-living elderly. We will assess the additional (health care) costs involved in INA and the costs per quality-adjusted life years (QALY) gained in the elderly and their informal caregivers. INA costs may be higher than expected because extra care and support are offered and more people could avail themselves of the services, or they may be lower than expected because specific groups of elderly and their informal caregivers will earlier and more purposefully avail themselves of the services and receive better support from their networks, preventing or delaying serious (health) problems. Delaying or preventing admission to a nursing home, for example, lowers costs and often appeals to the elderly and informal caregivers.

Health care utilization and given support will be quantified via questionnaires and additional sources where possible (Client Monitoring System, local and national monitors). Multiplying these volumes by integral cost prices will yield total costs of care and support. For this purpose we will use the guideline of the Dutch Health Care Insurance Board (CVZ) [38]. INA costs are estimated via time registrations on professionals' activity levels. Different types of activity (such as contact with the elderly and team meetings), professional disciplines, and corresponding tariffs will be taken into account. Assessment costs will be included in the total costs for the intervention group only and not the control group, because the costs are incurred only within the INA framework. Finally, costs per centre will be calculated (e.g., costs of the interventions, welfare, health care, community workers), providing insight for all participating organizations as to the investments that will be needed to continue INA after the study phase.

The cost-effectiveness evaluation will be on the basis of the costs and the registered effects described above. The primary analysis is a regular cost-utility analysis with differences between the intervention and control groups in costs and well-being (QALY) during a 12-month follow-up as outcome, allowing us to compare findings with other studies.

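### Death and moving are counted as sample loss, and no source is secured to record death or nursing-home admission equally in both groups, although avoided admission is a stated expected benefit

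*Protocol article*

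**What the plan says.** All passages are in the protocol article.

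- **Sample size.** "We will include 370 elderly (2/3 in intervention group, 1/3 in control group"). The authors "expect a loss of about 27% (by death, moving, no longer wishing to participate, etc.) between T0 and T2, resulting in a final sample of" participants numbering 270 (180 and 90), on whom the T2 comparison is sized. Home visits are the stated means of limiting loss.
- **II. Controlled pre-post measurement.** "All will be interviewed at home by experienced interviewers at three time-points": T0, 6 months and 12 months. Informal caregivers are interviewed twice by telephone.
- **Table 1.** Neither death nor loss of independent living is listed. The nearest entry is an 18-item health care utilization questionnaire.
- **Background.** Stronger networks are "expected to reduce the pressure on the healthcare system by preventing or delaying nursing home admissions".
- **iii. Costs.** "Delaying or preventing admission to a nursing home, for example, lowers costs and often appeals to the elderly and informal caregivers". The primary economic analysis is a 12-month cost-utility comparison. Utilization comes from questionnaires, plus other sources if these can be obtained (the Client Monitoring System, local and national monitors).
- **Weaknesses.** Utilization rests mainly on questionnaires to the elderly and their caregivers, with recall over three to six months, and not on insurer data.
- **I. Inventory.** The separate 24-month survey expects 70% response, "which includes a 15% attrition from death, relocation, institutional admission, et cetera". This is the only place where institutional admission is named as attrition.

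**The concern.** Death and a move to an institution are not ordinary non-response in this population. They are outcomes of frailty, and the article's own rationale expects INA to change one of them. Pooling them with refusal, and arranging follow-up around the home, means that the people who experience these events are the ones most likely to lack a T2 interview.

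Two results are exposed. The TFI contrast at T2 becomes a comparison of those alive and interviewed, and the two groups may be selected differently. The cost-utility comparison may miss institutional days and the QALYs lost after death. Matching on TFI, age and gender at entry does not protect against differences in exit afterwards. Imputation in a later analysis plan cannot restore an admission or death date that nobody collected.

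**Working it through.** **1. The plan's own figures.** Enrolment: "In total we expect to include 370 elderly (247 in the experimental group; 123 in the control group").
- 370 × (1 − 0.27) = 270.1, the stated 270.
- By group: 247 × 0.73 = 180.3 and 123 × 0.73 = 89.8, the stated 180 and 90.
- Expected loss: 247 − 180 = 67 INA and 123 − 90 = 33 control, 100 in all.

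The attrition arithmetic reproduces. The article does not divide these 100 people by cause.

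**2. Which source would record an admission or a death?**
- *Participant interview.* Planned at home. The text does not say whether it continues at a new address.
- *Caregiver call.* About 15 minutes, at T0 and T2. It does not depend on where the older person lives, but nothing says that every participant has a caregiver in the study, and Table 1 lists this utilization questionnaire (14 items) under caregiver outcomes. The items are not shown.
- *Client Monitoring System.* Under i. Process it registers client visits, assessments, goals and agreements within INA, so capture may be better in the INA group.
- *Local and national monitors.* Conditional on availability.

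With recall of three to six months, use up to T1 is captured for those interviewed at T1. An admission after T1 depends on the T2 interview or on one of these partial sources.

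**3. Admissions (assumed rates).** Suppose 12-month admission is 5% to 10% in controls and half that under INA.
- Control: 123 × 0.05 to 0.10 = 6.2 to 12.3 people. INA: 247 × 0.025 to 0.05 = 6.2 to 12.4 people.
- If all are lost before the stay is recorded, a true difference of 2.5 to 5 percentage points is observed as 0.
- If half are lost, with total control loss held at 27% and the same other loss in both groups, take the 5% case. Other loss = (0.27 − 0.025)/0.95 = 0.258. Observed control rate = 0.025/0.73 = 0.0342. Observed INA rate = 0.0125/(0.0125 + 0.975 × 0.742) = 0.0170. The difference is 1.7 points instead of 2.5. The 10% case gives 3.5 instead of 5.

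**4. TFI contrast.** If admitted people score g points higher (worse) than the rest and all are missing at T2, then

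shift = (difference in admission proportion) × g.

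- Differences of 0.025 to 0.05 with g of 2 to 4: 0.025 × 2 = 0.05 to 0.05 × 4 = 0.20.
- Wider assumptions, 0.03 to 0.10 with g of 3 to 5: 0.03 × 3 = 0.09 to 0.10 × 5 = 0.50.

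This works through admissions only, since the dead have no TFI.

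One-sided power at 180/90 with SD 3.0: standard error = 3.0 × √(1/180 + 1/90) = 0.387, and power = Φ(contrast/0.387 − 1.645).

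| Contrast among those interviewed | Power |
|---|---|
| 1.00 | 0.83 |
| 0.95 | 0.79 |
| 0.80 | 0.66 |
| 0.50 | 0.36 |

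These rows apply where the control group loses more such people. If the INA group does, the shift has the opposite sign.

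**5. Cost-utility (assumed, and only if no other source records the event).** With a between-group difference of 0.03 to 0.10:
- Institutional time, 6 months per admitted person: 0.03 × 6 = 0.18 to 0.10 × 6 = 0.6 months per person missing from the cost difference.
- Deaths at mid-year with utility 0.6: 0.03 × 0.5 × 0.6 = 0.009 to 0.10 × 0.5 × 0.6 = 0.03 QALY per person missing.

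**The case against.** The best defence is that a sample-size allowance is not an analysis rule. Inflating enrolment for expected loss is routine, and no passage excludes people who die or are admitted from the effect or cost analysis. Data analysis promises longitudinal and sensitivity analyses, and a condensed article may leave missing-data handling to a fuller document. This stands: the absence of an imputation plan is not the point here.

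Several stronger readings are tempting and are not supported:
- *Interviews take place only at home.* The text does not say only, nor that follow-up stops on admission.
- *Admission is defined as loss in the controlled comparison.* Sample size says moving. Institutional admission is named as attrition only for the inventory. That moving includes it is a natural inference for frail people over 70, but an inference.
- *Avoided admission is the main expected saving.* Costs gives it as one example, beside earlier and more purposeful service use and better network support.
- *Admission drops out of the cost results altogether.* Use up to T1, caregiver reports and the additional sources may capture part of it.
- *A real TFI benefit could be reversed.* The largest shift above is 0.50, half of the 1-point target.

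It is also fair that every rate used above is assumed, that Sample size applies the same 27% to both groups, and that admission is not itself one of the two central study questions.

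What the defence does not answer is data collection. Who counts as lost, where interviews are held and which outcomes are listed are stated choices. The fallback sources are conditional, and one of them is tied to the INA group.

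**Conclusion.** The concern holds in a limited form. As written, the plan can selectively lose participants who die or enter an institution, and it secures no record of these events that is equal in both groups, although it names avoided admission as a benefit and a saving. It does not follow that these people are excluded from the analysis or that the saving cannot be seen at all.

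Under the assumed rates the TFI contrast shifts by about 0.05 to 0.5 points, or 5% to 50% of the target. If INA prevents admissions, the shift works against INA. If INA signals problems earlier and leads to more admissions, it works in INA's favour. The economic figures (0.18 to 0.6 institutional months and 0.009 to 0.03 QALY per person) apply only where no other source records the event. The documents supply none of the admission rates, death rates, score gaps, lengths of stay or utilities. The point should be fixed, but it does not invalidate the design.

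**What to change.** Settle the following before follow-up starts, because a missed interview cannot be repeated:

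1. State that a move to an institution is not loss. Hold T1 and T2 at the new address, or by telephone or proxy.
2. For every participant in both groups, record date and type of exit (death, institutional admission, other move, withdrawal) by the same method.
3. In the cost-utility analysis, count utility 0 from the date of death and cost institutional days from the date of admission.
4. Report exits by group beside the TFI contrast, and state that the contrast is conditional on being alive and interviewed.

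A secondary outcome of being alive and living independently at 12 months is optional.

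The cost is one exit form, a few protocol sentences and some extra interviewer trips or calls. Interviews in institutions will be less complete. If exits are checked against the population register, a consent line may be needed: the article uses the register to sample the four inventory districts, whereas the controls come from comparable districts.
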